### Data monitoring and safety

An independent Data and Safety Monitoring Committee (DSMC), comprising a biostatistician, a rehabilitation physician, and a neurologist external to the study team, will review safety data after enrollment of the first 8 and 16 participants. Pre-specified stopping rules based on serious adverse event rates will be employed. Both tSCS and iTBS are generally well tolerated, with reported adverse events limited to transient skin irritation, paresthesia, mild muscle twitching, scalp discomfort, or headache (Lefaucheur et al., 2020; Moritz et al., 2024; Rossini et al., 2015). The risk of seizure with iTBS is very low (less than 0.1%) when appropriate screening and stimulation parameters are used (Lefaucheur et al., 2020; Rossini et al., 2015). Emerging studies combining spinal and cortical neuromodulation have not reported an increased incidence of adverse events, supporting the feasibility of combined application under careful monitoring (Lin et al., 2023; Pulverenti et al., 2022). The cardiovascular safety of cervical tSCS has been established in a secondary analysis of the Up-LIFT trial involving 60 participants, which showed that tSCS combined with rehabilitation did not adversely alter blood pressure regulation (Samejima et al., 2025).

## Results

This protocol will be submitted for ethical approval to the National Healthcare Group Domain Specific Review Board (NHG DSRB). Recruitment is expected to begin in the third quarter of 2026 at Alexandra Hospital, Singapore. Data collection is anticipated to be completed by the fourth quarter of 2027, with results expected to be published by mid-2028. As of the date of manuscript preparation, no participants have been enrolled.

## Discussion

### Principal considerations

This protocol describes the first controlled clinical trial designed to evaluate the combined application of cortical neuromodulation (iTBS) and spinal neuromodulation (tSCS), a convergent multi-level stimulation strategy, for upper limb recovery in chronic incomplete cervical SCI. The rationale is grounded in the complementary mechanisms of these two non-invasive modalities: iTBS enhances descending cortical drive by increasing excitability of the primary motor cortex and corticospinal projections above the injury, while tSCS primes sublesional spinal circuits by activating dorsal root afferents and raising the baseline excitability of motoneuron pools and spinal interneuronal networks below the injury (Fan et al., 2025; Singh et al., 2024). When these two sources of facilitation converge on alpha motoneurons and spinal interneurons, particularly during active task-specific training, the conditions for spike-timing-dependent plasticity and associative strengthening of residual corticospinal connections may be optimized.

### Comparison with prior work

The use of iTBS rather than conventional high-frequency rTMS represents a deliberate design choice informed by recent evidence and practical considerations. The standard iTBS protocol delivers 600 pulses in approximately 3–4 min, compared with 10–20 min for conventional 20 Hz rTMS, significantly reducing session burden and facilitating integration into clinical rehabilitation workflows. Recent trials by Feng et al. (2023) and Shi et al. (2026) have demonstrated the efficacy of iTBS in SCI populations, and the Patel et al. (2025) protocol, also published in JMIR Research Protocols, provides further methodological precedent for iTBS-based studies in this population.

The choice of a two-arm design (combined versus tSCS alone) rather than a four-arm factorial design reflects the pilot nature of this study. While a factorial design would enable disentangling of individual and combined effects, the sample size required would be prohibitive for a first-in-class pilot. The present design is optimized to address the pragmatic clinical question of whether adding iTBS to tSCS-based rehabilitation provides incremental benefit, which is the most relevant question for clinical decision-making in settings where tSCS is increasingly being implemented. Data from this pilot will inform whether a larger factorial trial is warranted.

We acknowledge that activity-based restorative therapy literature typically favors 3–5 sessions per week, and that the 3–4 day inter-session gaps in our protocol may attenuate the cumulative spike-timing-dependent priming effects that denser schedules could achieve. This introduces a risk of Type II error should the intervention prove effective only at higher densities. We have retained the twice-weekly schedule because (i) the total dose of 24 sessions matches the Up-LIFT trial, enabling cross-study comparison; (ii) iTBS after-effects on cortical excitability persist beyond single sessions and may partially bridge inter-session gaps; (iii) feasibility and retention are primary pilot objectives; and (iv) most participants in our outpatient setting rely on caregiver-assisted transport, making thrice-weekly attendance impractical. Session density will be explicitly re-evaluated as a design parameter for the subsequent confirmatory trial, and pilot effect-size estimates should be interpreted as a lower bound on achievable benefit. The inclusion of a 12-week post-intervention follow-up extends beyond the single 4-week follow-up used in some prior studies, providing more robust data on durability of treatment effects.

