### Randomization and allocation concealment

Participants will be randomized in a 1:1 ratio using a computer-generated, permuted block randomization schedule (block sizes of 4 and 6, randomly varied) stratified by AIS grade (C versus D) and baseline UEMS on the more impaired side (10–14 versus 15–20). The randomization schedule will be generated by an independent biostatistician at the Clinical Research & Innovation Office, Tan Tock Seng Hospital, with no direct involvement in participant recruitment or assessment, and stored in a secure, web-based centralized randomization system (REDCap Randomization module). Allocation concealment will be ensured by sequential, opaque, sealed envelopes accessible only to the unblinded intervention therapist.

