#### Sample size

This is an exploratory pilot trial, and the sample size of 24 participants (12 per group) is based primarily on feasibility considerations and is consistent with recommendations for pilot studies in neuromodulation and SCI rehabilitation (Julious, 2005). This sample size is sufficient to estimate the standard deviation of the primary outcome, assess feasibility parameters, and generate preliminary effect size estimates with reasonable precision to inform the power calculation for a subsequent confirmatory trial. Assuming 20% attrition, we aim to enroll 24 participants to ensure at least 10 evaluable participants per arm. This is consistent with sample sizes in comparable neuromodulation pilot trials in SCI (Feng et al., 2023; Gharooni et al., 2018; Lin et al., 2023).

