### Statistical analysis

All analyses will follow the intention-to-treat (ITT) principle, defined as all randomized participants who receive at least one treatment session and have at least one post-baseline assessment. Continuous variables will be summarized as mean and standard deviation (or median and interquartile range where appropriate). Between-group comparisons for the primary outcome (UEMS change from baseline to week 12) will be analyzed using a linear mixed-effects model with treatment group, time, and treatment-by-time interaction as fixed effects, stratification factors (AIS grade and baseline UEMS) as covariates, and participant as a random effect. An unstructured covariance matrix will be assumed for repeated measures.

Secondary continuous outcomes will be analyzed using analogous mixed-effects models. Effect sizes (Cohen d) and 95% confidence intervals will be reported for all between-group comparisons to support the planning of a future definitive trial. A per-protocol analysis (participants completing 20 or more of 24 sessions) will be conducted as a sensitivity analysis. Missing data will be handled within the mixed-effects framework under the assumption of missing at random (MAR). Feasibility outcomes will be reported descriptively against the pre-specified progression criteria. A sensitivity analysis excluding participants with antispasticity dose changes will be conducted for the Modified Tardieu Scale outcome. Safety outcomes will be tabulated by treatment group with frequencies and proportions. All analyses will be performed using R (version 4.3 or later), with statistical significance set at P < .05. All between-group efficacy comparisons (primary and secondary) will be reported as exploratory. The trial’s primary purpose is estimation of effect sizes, variability, and feasibility parameters for a definitive trial. Secondary functional and neurophysiological outcomes carry elevated Type I error risk due to multiple testing without correction and should be interpreted as hypothesis-generating only.

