### Limitations

Several limitations should be acknowledged. First, the pilot sample size of 24 participants (12 per group) limits statistical power for detecting small to moderate between-group differences and precludes definitive efficacy conclusions. This is mitigated by the explicit pilot framing and the pre-specified feasibility progression criteria. Second, the single-center design at Alexandra Hospital may limit generalizability, although it enhances protocol fidelity and reduces inter-site variability. Third, the assessor-blinded (rather than double-blinded) design introduces the possibility of performance bias, as participants in the experimental arm are aware of receiving iTBS. However, assessor blinding will be rigorously maintained, and all primary and secondary outcomes are either clinician-assessed or objective measures. Fourth, the heterogeneity inherent in the SCI population, including variations in injury level, completeness, and chronicity, may introduce variability in treatment responses; the stratified randomization is designed to address this concern. Fifth, the absence of a standalone iTBS arm means that the independent contribution of iTBS cannot be isolated from its interaction with tSCS, although this was a deliberate design choice to maximize the clinical relevance of the comparison for a pilot study.

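### The protocol tells readers to take the pilot effect size as a lower bound on benefit, but sampling error alone rules that out and unblinded participants leave the direction of bias unknown

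*Protocol article*

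**What the plan says.** Comparison with prior work (Discussion) explains why two sessions a week were kept, and accepts that longer gaps between sessions may weaken the cumulative effect. It ends with an instruction to the reader: "pilot effect-size estimates should be interpreted as a lower bound on achievable benefit". No other reason is given.

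Sample size says that the number of participants "is based primarily on feasibility considerations". It adds that this number is enough to "generate preliminary effect size estimates with reasonable precision to inform the power calculation for a subsequent confirmatory trial", without giving an interval width, a standard deviation or a precision target. On numbers it says: "Assuming 20% attrition, we aim to enroll 24 participants to ensure at least 10 evaluable participants per arm".

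Statistical analysis makes the estimation of effect sizes, variability and feasibility parameters for a definitive trial the main purpose. It calls all efficacy comparisons exploratory and promises intervals: "Effect sizes (Cohen d) and 95% confidence intervals will be reported for all between-group comparisons".

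Blinding states that control participants will know they are not receiving iTBS and that there is no sham. Assessors are blinded. Limitations concedes that the design "introduces the possibility of performance bias, as participants in the experimental arm are aware of receiving iTBS".

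**The concern.** A point estimate is a lower bound only if something keeps it below the quantity of interest. The article offers one influence that may pull it down, the session schedule. It leaves out sampling error, which is large at this size and acts in both directions. It also leaves out the possible performance bias that the article itself reports under Limitations. UEMS is graded voluntary strength, so a participant's effort enters the score even when the assessor does not know the arm.

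The sentence is an instruction on how to use the estimate that the trial exists to supply. A reader who follows it would treat the pilot d as the least that can be expected when planning the confirmatory trial.

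**Working it through.** **Inputs.** From Sample size: 12 per arm enrolled and at least 10 per arm evaluable. From Randomization and allocation concealment: "Participants will be randomized in a 1:1 ratio". From Statistical analysis: "statistical significance set at P < .05", Cohen d and 95% confidence intervals. The sidedness of the test is not stated; two-sided is assumed, to match the intervals. The article gives no SD for UEMS change, so results are in SD units first.

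**The plan's own figure.** Taking 20 evaluable in total, 20 × 1.2 = 24, the stated enrolment. Dividing by the retained fraction gives 20 / 0.8 = 25, and 12 × 0.8 = 9.6 per arm, just under 10. The stated figure is close enough, and 10 to 12 per arm is the right range to examine. No power or precision figure is stated, so there is none to reproduce.

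**Half-width of the 95% interval**, unadjusted difference in SD units: t(0.975, 2n − 2) × √(2/n).

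- n = 12: 2.074 × √(2/12) = 0.85 SD
- n = 10: 2.101 × √(2/10) = 0.94 SD

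**Exact interval for an observed d** (noncentral t, with t = d × √(n/2)):

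| Observed d | 12 per arm | 10 per arm |
|---|---|---|
| 0.5 | -0.32 to 1.31 | -0.40 to 1.38 |
| 0.8 | -0.04 to 1.63 | -0.12 to 1.70 |

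The statistical lower bound is the lower limit of the interval. In both rows it is below zero.

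**How often the estimate exceeds the benefit it is meant to bound.** Let the true d be 0.5, let a denser schedule multiply it by k, and let bias from unblinded participants add b. The probability is 1 − F(k × d × √(n/2)), where F is the noncentral t distribution with 2n − 2 degrees of freedom and noncentrality (d + b) × √(n/2). The values of d, k and b are assumptions; the article gives none.

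| k | b (SD) | 12 per arm | 10 per arm |
|---|---|---|---|
| 1.00 | 0 | 51% | 51% |
| 1.25 | 0 | 39% | 40% |
| 1.50 | 0 | 28% | 30% |
| 1.25 | 0.2 | 58% | 57% |
| 1.50 | 0.2 | 46% | 47% |

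Even the most favourable row, a 50% gain from density and no bias, leaves the estimate above the achievable benefit in more than a quarter of trials.

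**On the UEMS scale**, for an assumed SD of change (12 and 10 per arm): SD 2 gives a half-width of 1.7 and 1.9 points; SD 3 gives 2.5 and 2.8; SD 4 gives 3.4 and 3.8; SD 6 gives 5.1 and 5.6. From SD 3 upwards the half-width exceeds the 2-point difference named under Hypotheses.

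**The case against.** The strongest reply is that the sentence closes a paragraph on session density. Achievable benefit then most naturally means benefit under a denser schedule, and lower bound is a loose way of saying attenuated. That reading is fair, and it means that the 51% row is not the right comparison. The rows with k above 1 are, and they still show the estimate above the benefit in 28 to 40% of trials without any bias. The reply explains the sentence but does not make it correct.

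The article also does not ignore expectation. It uses neutral consent framing and enters a credibility and expectancy questionnaire as a covariate in sensitivity analyses. These measures may reduce the bias; they do not show that it is absent or downward.

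Four stronger readings are tempting, and the documents do not support them.

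- **The precision claim is false.** It is qualitative, applies to estimates called preliminary, and sits beside promised intervals, an exploratory label and an admission of limited power. It is generous wording with no threshold to fail.
- **The trial is open-label.** It is assessor-blinded; participants and the treating therapist are not blinded.
- **The pilot estimate is inflated.** Limitations gives performance bias no direction or size. Upward bias is plausible, not shown.
- **The next trial will be underpowered or started on noise.** The article says only that the pilot will inform its design and powering. None of the five progression criteria under Feasibility outcomes uses an effect size.

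Finally, the half-widths are unadjusted. The planned mixed model adjusts for AIS grade and baseline UEMS, which may narrow the interval in UEMS points by an amount the article does not let anyone calculate.

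**Conclusion.** The point holds for the lower-bound statement, which is wrong as written under either reading of achievable benefit. It rests on one possible downward influence and passes over sampling error of about 0.85 to 0.94 SD either way, as well as a possible bias that the article itself concedes. The net direction cannot be known from the documents.

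The half-widths and the intervals for d assume only equal arms of 10 to 12, a common SD and an unadjusted comparison. The exceedance percentages depend further on the assumed true d of 0.5, density gain and bias; they illustrate the point and are not estimates for this trial.

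The precision phrase under Sample size needs a number beside it and is otherwise a matter of emphasis. No endpoint, model, sample size or progression decision is affected. What changes is what may be concluded from the effect estimate, which is part of the stated main purpose.

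**What to change.** In Comparison with prior work, delete the lower-bound statement. Say instead that the schedule may attenuate the effect, that the lack of participant blinding may inflate it, and that the net direction is unknown.

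In Sample size, replace or qualify the precision phrase with the expected 95% half-width: about 0.85 SD with 12 per arm and 0.94 SD with 10, unadjusted. Add that covariate adjustment may narrow it on the UEMS scale. Add also that the pilot point estimate will not be used alone, or as a floor, to power the confirmatory trial, for which the 2-point difference under Hypotheses is available as the target.

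The cost is a few sentences. The stated precision will look less favourable. Nothing in the conduct of the trial changes.

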### Strengths

Several methodological strengths distinguish this protocol. First, the comprehensive outcome battery spans multiple domains of the International Classification of Functioning, Disability and Health (ICF) framework: motor impairment (UEMS, GRASSP-2, grip/pinch strength), fine and gross motor dexterity (Nine-Hole Peg Test, Box and Block Test), functional capacity (CUE-T), independence (SCIM-III), spasticity (Modified Tardieu Scale), neurophysiology (CMCT, MEPs, EMG), quality of life (EQ-5D-5L), and patient-centered goals (Modified GAS). Second, the inclusion of CMCT and MEP assessments provides mechanistic insight into whether the combined intervention produces measurable changes in corticospinal tract integrity and excitability. Third, the standardized tSCS protocol, informed by the largest published dataset on cervical tSCS programming (Gelenitis et al., 2025), enhances reproducibility and comparability with the existing evidence base. Fourth, the inclusion of the EQ-5D-5L enables future health economic evaluation of the combined intervention. Fifth, the study is situated in a Southeast Asian rehabilitation center, extending the evidence base beyond North American and European settings where the majority of tSCS research has been conducted.

### Limitations

Several limitations should be acknowledged. First, the pilot sample size of 24 participants (12 per group) limits statistical power for detecting small to moderate between-group differences and precludes definitive efficacy conclusions. This is mitigated by the explicit pilot framing and the pre-specified feasibility progression criteria. Second, the single-center design at Alexandra Hospital may limit generalizability, although it enhances protocol fidelity and reduces inter-site variability. Third, the assessor-blinded (rather than double-blinded) design introduces the possibility of performance bias, as participants in the experimental arm are aware of receiving iTBS. However, assessor blinding will be rigorously maintained, and all primary and secondary outcomes are either clinician-assessed or objective measures. Fourth, the heterogeneity inherent in the SCI population, including variations in injury level, completeness, and chronicity, may introduce variability in treatment responses; the stratified randomization is designed to address this concern. Fifth, the absence of a standalone iTBS arm means that the independent contribution of iTBS cannot be isolated from its interaction with tSCS, although this was a deliberate design choice to maximize the clinical relevance of the comparison for a pilot study.

## Conclusion

This pilot randomized controlled trial will provide the first controlled evidence on whether adjunctive cortical neuromodulation via iTBS enhances upper limb motor recovery beyond tSCS-based rehabilitation alone in individuals with chronic incomplete cervical SCI. The feasibility data, effect size estimates, and safety profile generated will directly inform the design and powering of a subsequent multicenter confirmatory trial. By targeting both supraspinal and spinal levels of the motor neuraxis with non-invasive stimulation alongside structured rehabilitation, this convergent neuromodulation approach has the potential to advance the therapeutic landscape for individuals with tetraplegia who face substantial unmet clinical need.
